### 2.5. Study Variables

Sociodemographic variables (age, sex and place of residence) will be measured in all participants.

BMI: The quotient of weight (kg) and height^2^ (m). BMI will be categorised according to the age and gender cut-off points defined by the World Health Organization in underweight (<18.5 kg/m^2^), normal weight (18.5–24.9 kg/m^2^) and overweight/obesity (≥25 kg/m^2^) [43].

Body fat percentage: A calibrated multifrequency signal bioimpedance meter with electrodes on the feet and a grip on both hands will be used for measurement. The participant will remain barefoot with the heels and soles of the feet located on the sensors of the equipment and the grip of the hands in the most appropriate grip position for their height. The bioimpedance analysis will be performed after a fast of at least 5 h, without having performed physical exercise or ingested alcohol in the previous 48 h and having previously emptied the urinary bladder—Seca-770 (SECA Gmbh & Co. Kg, Hamburg, Germany).

Muscle strength: Measured with a Takei TKK 5101 (Takei Scientific Instruments Co., Ltd., Tokyo, Japan) dynamometer, the muscular strength will be categorised as excellent, good, medium, bad or very bad. Muscular strength will be dichotomised, taking the cut-off point of the 25th percentile, by sex.

CPR quality: Upon performing the CPR manoeuvre, on the basis of previous studies [44,45], quality CC (Q-CC) will be evaluated via the following formula:Q-CC (%) = [% CCcD + % CCcR + % CCchR]/3.(1)In the equation, CCcD is the CC with correct depth (between 5 and 6 cm), CCcR is the CC with correct rhythm (100-/min) and CCchR is the CC with complete chest re-expansion.

Effective ventilation (EV) is evaluated asEV (%) = (NEV × 100)/NTV(2)
where NEV is the number of effective ventilations and NTV is the total number of ventilations.

These parameters are based on the ERC-2021 [9] recommendations and are recorded by phantom software (Laerdal Resusci Anne CPR-D and SkillRepoter^®^; Medical Laerdal; Stavanger, Norway).

Adequate self-perception of CC and ventilations: Asking the participants if they think they have performed them correctly, with the possible answers being CC: YES/NO, V: YES/NO.

The results will be tabulated at different altitudes.

SO_2_m: This will be measured with near-infrared spectrophotometry in biceps brachii and erector spinae. The data will be categorised into four phases: baseline, phase close to fatigue, the fatigue phase and the recovery phase—Humon Hex® (Humon Inc., Cambridge, MA, United States).

VO_2_max: Using ergospirometry, this will be categorised as very bad, bad, medium, good and very good level of cardiorespiratory fitness. It will be measured with a treadmill ergometer (HP-Cosmos, mod. Pulsar 3P) (h/p/cosmos sports & medical GmbH, Nussdorf-Traunstein, Germany), Cardinal Health electrocardiograph mod. Ergoline ER800 (ergoline GmbH, Bitz, Germany) and an automatic breathing gas analysis system (mod. Oxycom Alpha-Jaeger) (Erich Jaeger GmbH, Höchberg, Germany).

Cardiorespiratory fitness will be dichotomised as higher and lower using the Cooper Institute cut-off points for 20–30-year-old adults (VO_2_max ≥38 mL/kg/min for women and ≥43 mL/kg/min for men) [46].

Blood determinations: Before the start and after the completion of each test (pre and post) Hgb, Hct, Mb, and lactate levels in venous blood will be determined with Epoc^®^ Blood Analysis System devices (Siemens Healthineers, Ottawa, ON, Canada).

RPE: At the end of each of the CPR tests, the participants will be asked to rate the perception of the effort made using the Borg scale. It consists of numbers from 6 to 20, where each number represents a level of perceived exertion. The number 6 on the scale is associated with very light effort, whereas the number 20 is associated with maximum effort. The intermediate numbers on the scale represent increasing levels of perceived exertion [47].

Anxiety levels: The State–Trait Anxiety Inventory (STAI) questionnaire will be used [48]. This questionnaire measures anxiety in healthy adults. It consists of two scales: SA (which reflects the subjective and transitory feelings of tension, apprehension and fear that can vary with time and fluctuate in intensity) and TA (which reflects a relatively stable anxious propensity that characterises individuals with a tendency to perceive situations as threatening). The questionnaire provides a numerical value for the TA and another for the SA. The total STAI is the sum of SA and TA. Each subscale is made up of a total of 20 items in a 4-point Likert response system according to intensity (0 = almost never/not at all; 1 = somewhat/sometimes; 2 = quite/often; 3 = a lot/almost always). The total score for each of the subscales ranges from 0 to 60 points. STAI-TA will be administered at the beginning of the investigation and STAI-SA at the end of pre-conditioning and post-conditioning CPR at 670 m asl and 5000 m asl.

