The main aim of the study is to analyse the effect of reducing the fraction of inspired oxygen (FiO_2_) at medium and high altitudes (3000 and 5000 m asl) on the quality of the basic CPR performed on adults. The secondary objectives are (a) to assess the perception of effort and levels of anxiety involved in performing CPR at these altitudes; (b) to determine whether there is an association between altitude, body mass index (BMI) and physical fitness and the proportion of correct CCs achieved at the proposed altitudes; (c) to analyse the muscle oxygen saturation (SmO_2_) values during CPR at the proposed altitudes; (d) to determine the blood variations produced (lactate, haematocrit (Hct), haemoglobin (Hgb), creatine phosphokinase (CPK), and myoglobin (Mb)); and (e) to assess the quality of the CPR components (CCs and ventilations), the ratings of perceived exertion (RPE), and associations between BMI, SmO_2_ and anxiety levels at 670, 3000 and 5000 m asl after an adaptation programme to intermittent hypoxia.

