### 2.6. Statistical Analysis

First, a descriptive analysis of the study variables will be carried out, along with the appropriate tabulation and graphical representation of the data. Qualitative variables will be expressed as proportions with 95% confidence intervals, and quantitative variables will be described using means and standard deviations or medians and interquartile ranges, as appropriate. Prior to the application of parametric tests, the assumption of normality will be assessed for all continuous variables using the Shapiro–Wilk test.

For comparisons involving paired quantitative data, Student’s *t*-test for paired samples will be used when the normality assumption is met. If this assumption is violated, the non-parametric Wilcoxon signed-rank test will be applied.

For between-group comparisons (intervention vs. control), independent-sample t-tests will be used for normally distributed variables, while the Mann–Whitney U test will be used for non-normally distributed variables.

To evaluate the effect of the intervention across time and altitude conditions, a mixed-model ANOVA will be used, including group (intervention vs. control) as a between-subject factor and time (pre vs. post) and altitude as within-subject factors.

For categorical variables, McNemar or chi-square tests will be applied as appropriate.

A multivariate linear regression analysis will be performed to adjust for potential confounding variables (age, sex, BMI, and physical fitness), including group allocation as an independent variable. Model assumptions (normality, homoscedasticity, and independence of residuals) will be checked.

Statistical significance will be set at *p* < 0.05. All statistical analyses will be performed using IBM^®^ SPSS^®^ Statistics 28 software.

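### The anxiety total adds a trait score taken once at entry to each post-CPR state score; naming STAI-SA as the outcome and adjusting for entry STAI-TA would be a minor, free improvement

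*Protocol article*

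**What the plan says.** The anxiety paragraph of section 2.5 treats the two scales as different in kind. SA is a passing feeling that fluctuates. TA is "a relatively stable anxious propensity that characterises individuals with a tendency to perceive situations as threatening". On scoring it says "The questionnaire provides a numerical value for the TA and another for the SA", then adds "The total STAI is the sum of SA and TA". On range: "The total score for each of the subscales ranges from 0 to 60 points".

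The scales are given at different times. "STAI-TA will be administered at the beginning of the investigation", whereas the state scale is scheduled as "STAI-SA at the end of pre-conditioning and post-conditioning CPR at 670 m asl and 5000 m asl". That is one trait score and four state scores per participant.

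Secondary objective (a), at the end of the Introduction, is "to assess the perception of effort and levels of anxiety involved in performing CPR at these altitudes". Objective (e) adds associations between BMI, muscle oxygen saturation and anxiety after the conditioning programme. Neither objective says which STAI score is meant.

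Section 2.6 names no anxiety score either. It plans four kinds of analysis that could apply to one:
- paired tests ("For comparisons involving paired quantitative data", a t-test or Wilcoxon signed-rank);
- unadjusted independent-sample tests between groups (t-test or Mann–Whitney);
- a mixed ANOVA with group, time and altitude;
- a linear regression adjusting for age, sex, BMI and fitness.

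Trait anxiety is not among the listed adjustment variables.

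**The concern.** Both objectives ask how anxious people are when they perform CPR at altitude, or after conditioning. A trait score taken at entry cannot respond to either. Adding it to each later state score therefore brings in nothing about altitude or conditioning that SA does not already hold.

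The damage depends on the comparison. In contrasts within a person the addition is harmless but pointless. In comparisons between people it matters in two ways. It widens the spread of the outcome without adding to the group difference, and it lets a link between trait anxiety and, say, BMI show up as a link with anxiety about the test.

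Because the article leaves the anxiety score open, SA, TA and the total are all available when results are read. The entry TA score also has a better use, as a baseline covariate for SA, which the article does not mention.

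**Working it through.** **Inputs from the protocol article.** Total = SA + TA; TA once at entry; SA at four occasions (section 2.5). Allocation is 1:1 (section 2.3), so 56 analysed participants give 28 per arm. Significance level 0.05 (section 2.6), taken as two-sided.

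**Assumptions, not in the article.** The SA–TA correlation ρ and the ratio k = SD(TA)/SD(SA). The article gives no power or variance figure for anxiety, so there is none to reproduce.

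**1. Change within a person.** For any two occasions,

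(SA₂ + TA) − (SA₁ + TA) = SA₂ − SA₁.

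The paired differences are identical, so the paired t-test and the signed-rank test are identical too. The same holds for the time, altitude and interaction terms of the mixed ANOVA, which are built from such differences. A simulated data set (56 people, four occasions) confirmed it. The group-by-time contrast gave t = 0.940, p = 0.351 for both SA and the total. The paired altitude contrast gave t = 0.450, p = 0.655 for both.

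**2. Group comparison at one occasion.** Here TA does not cancel. With SD(SA) = 1,

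Var(total)/Var(SA) = 1 + k² + 2ρk, which is 2 + 2ρ when k = 1.

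Adjusting SA for entry TA instead leaves a residual variance of 1 − ρ².

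The difference with 80% power on unadjusted SA is (1.960 + 0.842) × √(2/28) = 0.749 SD(SA), by the normal approximation. TA precedes the intervention, so the expected group difference on the total is the same 0.749. Power is Φ(0.749 / (s × √(2/28)) − 1.960), where s is the square root of the variance factor. For k = 1:

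| ρ | Variance factor, total | Power, total | Variance factor, SA adjusted for TA | Power, SA adjusted for TA |
|---|---|---|---|---|
| 0 | 2.0 | 51% | 1.00 | 80% |
| 0.3 | 2.6 | 41% | 0.91 | 84% |
| 0.5 | 3.0 | 37% | 0.75 | 90% |
| 0.7 | 3.4 | 33% | 0.51 | 97.5% |

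Varying k from 0.75 to 1.25 and ρ from 0 to 0.7, the variance factor of the total runs from 1.6 (1 + 0.5625 + 0) to 4.3 (1 + 1.5625 + 1.75).

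The table covers an unadjusted test at one occasion. The group main effect of the mixed ANOVA also retains TA, but it averages over occasions, so these figures do not carry over to it.

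**3. Associations with BMI or muscle oxygen saturation.** Let X be either variable and k = 1.
- If X is related to SA (correlation r) and not to TA, its correlation with the total is r/√(2 + 2ρ). That is 0.62r, 0.58r and 0.54r for ρ = 0.3, 0.5 and 0.7.
- If X is related to TA (correlation r) and not to SA, its correlation with the total is again r/√(2 + 2ρ), although its correlation with the state score is zero.

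**The case against.** The strongest reply is that the sentence on the total describes how a questionnaire is scored, not what will be analysed. The sentence before it gives separate values for the two scales, the schedule treats them separately, and the Introduction reports earlier CPR work as separate trait and state results. Neither the objectives nor section 2.6 mentions the total. This stands: a reader might infer that the trial will test its anxiety objectives on the total and lose about half its power, but the article does not say so.

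A reader might also infer that the total adds noise to every anxiety analysis. It does not. Step 1 of the working shows that it cannot in the paired tests or in the within-person and interaction terms, and section 2.6 assigns the effect of the intervention over time and altitude to the mixed ANOVA.

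Third, leaving TA off the covariate list is not an error. The only dependent variable named for the regression, in section 2.3, is change in compression quality, so the list is not shown to govern an anxiety model. Choice of covariates for a secondary outcome is often left to the analysis plan. This also stands.

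What remains is that the article does define the total among its study variables, leaves open which score answers objectives (a) and (e), and plans unadjusted between-group tests although a suitable baseline covariate is already collected.

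**Conclusion.** A minor point on a secondary objective; the primary aim, the sample size and the data to be collected are untouched. The total is redundant with SA for change within a person. In between-group comparisons at one occasion and in associations it is inferior to SA, because it carries trait variance and no treatment signal.

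That direction follows from the definitions alone. The size does not. The variance factor of 2.6 to 3.4 and the fall from 80% to 41–33% power assume equal SDs, ρ of 0.3 to 0.7, 28 analysed per arm and an unadjusted single-occasion test. They show what using the total there would cost, not a loss that the trial is known to face.

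The gain from adjusting SA for TA likewise depends on ρ and vanishes at ρ = 0. It would probably be smaller than tabulated once pre-conditioning SA is also in the model, since that score already reflects part of the trait.

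**What to change.** - Name STAI-SA as the anxiety outcome for objectives (a) and (e), and state that the total is not used as an outcome. Report entry STAI-TA as a baseline characteristic.
- For the group comparison of post-conditioning SA, replace the unadjusted independent-sample test with a linear model containing group, entry STAI-TA and pre-conditioning SA at the same altitude.
- In models relating post-conditioning SA to BMI or muscle oxygen saturation, include entry STAI-TA as a covariate.
- Leave the analyses of within-person change as they are; they need no trait covariate.

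The cost is two or three sentences and one or two degrees of freedom per model. Every score needed is already scheduled.

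### State anxiety is not scheduled at 3000 m, although secondary objectives (a) and (e) cover that altitude; as a lesser point, no CPK measurement is described although objective (d) lists it

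*Protocol article*

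**What the plan says.** **Anxiety.** The Introduction of the protocol article sets the altitudes of the main aim at 3000 and 5000 m. Secondary objective (a) refers back to them: "to assess the perception of effort and levels of anxiety involved in performing CPR at these altitudes". Secondary objective (e) names the altitudes itself and includes "associations between BMI, SmO_2_ and anxiety levels at 670, 3000 and 5000 m asl after an adaptation programme to intermittent hypoxia".

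Section 2.5 (Anxiety levels) gives the measurement schedule. The trait scale is given once, at the start. The state scale is given as "STAI-SA at the end of pre-conditioning and post-conditioning CPR at 670 m asl and 5000 m asl".

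Section 2.4 describes six CPR tests per participant. Stage 2 has M1 (670 m), M2 (3000 m) and M3 (5000 m); Stage 4 has P1, P2 and P3 at the same altitudes.

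**Blood.** Objective (d) concerns blood variations and lists "lactate, haematocrit (Hct), haemoglobin (Hgb), creatine phosphokinase (CPK), and myoglobin (Mb". Section 2.5 (Blood determinations) states that, before and after each test, "Hgb, Hct, Mb, and lactate levels in venous blood will be determined" with a named point-of-care device.

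**The concern.** The objectives and the measurement schedule do not match. Two secondary objectives ask about anxiety at an altitude where the plan collects no state-anxiety score. State anxiety is a momentary response, taken at the end of a test. If it is not recorded after the 3000 m tests, it cannot be reconstructed later.

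A team following section 2.5 exactly would finish with anxiety data at only one of the two simulated altitudes in objective (a), and at two of the three altitudes in objective (e). The likely result is a report on anxiety at altitude that rests on 5000 m alone, or a stated outcome that goes unreported without explanation.

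The CPK discrepancy is of the same kind but weaker. An analyte is promised in an objective, and no measurement of it is described.

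**Working it through.** No sample-size, power or error-rate figure enters this point. The check sets the objectives against the schedule and counts.

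**Step 1: state anxiety, test by test** (tests from section 2.4, Stages 2 and 4; schedule from section 2.5)

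| Test | Altitude | Conditioning | STAI-SA scheduled | RPE scheduled |
|---|---|---|---|---|
| M1 | 670 m | before | yes | yes |
| M2 | 3000 m | before | **no** | yes |
| M3 | 5000 m | before | yes | yes |
| P1 | 670 m | after | yes | yes |
| P2 | 3000 m | after | **no** | yes |
| P3 | 5000 m | after | yes | yes |

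STAI-SA is scheduled at 4 of 6 tests, so 6 − 4 = 2 tests lack it. Both are the 3000 m tests.

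**Step 2: what each objective needs**
- Objective (a) needs anxiety at 3000 and 5000 m. Before conditioning these are M2 and M3; M2 is missing.
- Objective (e) needs anxiety at 670, 3000 and 5000 m after conditioning. These are P1, P2 and P3; P2 is missing.

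**Step 3: can another measure fill the gap?**
- The trait scale is given once, is not tied to any test, and is described in section 2.5 as a relatively stable propensity. It cannot show a response to altitude.
- RPE is collected after every CPR test, but it measures effort. It also shows that the gap is specific to STAI-SA: objective (a) pairs effort with anxiety, and only effort is recorded at 3000 m.
- The Abstract says that anxiety will be measured at different altitudes. That fits two altitudes as well as three and settles nothing.
- The Figure 1 legend lists STAI without time points. The figure itself is not available here, but it could not remove the conflict between two explicit texts.

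**Step 4: blood analytes**

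| Analyte in objective (d) | Described in section 2.5 |
|---|---|
| Lactate | yes |
| Haematocrit | yes |
| Haemoglobin | yes |
| Myoglobin | yes |
| CPK | **no** |

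Four of the five analytes have a described measurement. Outside objective (d), CPK appears only in the Abbreviations list, without method, device or time point.

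**The case against.** **The two altitudes may be deliberate.** Measuring state anxiety only at the lowest and highest altitude limits participant burden, and objective (a) asks only that levels be assessed. On that view the objectives are loosely worded and the remedy is editorial. This is a fair possibility, and the fix allows for it. It does not remove the inconsistency: objective (e) names 3000 m explicitly, objective (a) includes it by reference, and no reason is given for omitting it.

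**The full protocol may resolve it.** For state anxiety this carries little weight, because section 2.5 gives a specific schedule rather than leaving one out. For CPK it carries more. Section 2.5 lists what the named device determines and does not claim to list every blood assay, so a CPK assay by another method could have been dropped when the article was condensed. A reader might infer that CPK is not measured at all. The text supports only the statement that no CPK measurement is described.

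**Most of the three objectives survives.** A reader might conclude that objectives (a), (d) and (e) cannot be answered. That goes too far. RPE is available at every altitude, anxiety at 670 and 5000 m before and after conditioning, and four of the five analytes before and after each test. The CPR-quality, BMI and muscle-oxygen parts of (e) are untouched.

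**The mixed-model ANOVA still runs.** A reader might also infer a conflict with section 2.6, which uses altitude as a within-subject factor. There is none. That section does not say that every outcome must have three altitude levels, and with two levels the model can be fitted to STAI-SA. It simply estimates nothing at 3000 m.

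**Conclusion.** The point holds in a limited form. If section 2.5 is followed as written, the 3000 m anxiety part of secondary objectives (a) and (e) has no data: 2 of 6 tests, M2 and P2. The loss is permanent once those tests are over. The main aim, RPE, and anxiety at 670 and 5000 m are unaffected. The point concerns the completeness of two secondary objectives and implies no bias or loss of power elsewhere.

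This rests on two readings: that the altitudes in objective (a) are the 3000 and 5000 m of the main aim, and that the STAI-SA schedule in section 2.5 is complete. Both follow the plain wording.

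The CPK discrepancy is a lesser point about reporting. It concerns one of five analytes, and the documents leave open whether an assay is planned but undescribed.

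**What to change.** **State anxiety, one of two routes:**
1. Add STAI-SA at the end of M2 and P2, and amend section 2.5 to list all three altitudes. The cost is one 20-item questionnaire at each of two tests already planned, a small added burden. This route lets the trial answer objectives (a) and (e) as written. It must be in place before the tests are run; if 3000 m tests have already taken place without the scale, their data cannot be recovered.
2. If two altitudes are intended, remove 3000 m from the anxiety part of objectives (a) and (e). The cost is a text edit. The study then makes no statement on anxiety at 3000 m.

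**CPK:** either state the assay, device and time points in section 2.5, or delete CPK from objective (d). Deletion is a text edit. The cost of measuring CPK cannot be judged from the article: it does not say whether the named device can determine it or whether the planned pre- and post-test samples would suffice. It should not be assumed to be a cheap addition to the existing draws.

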### 2.6. Statistical Analysis

First, a descriptive analysis of the study variables will be carried out, along with the appropriate tabulation and graphical representation of the data. Qualitative variables will be expressed as proportions with 95% confidence intervals, and quantitative variables will be described using means and standard deviations or medians and interquartile ranges, as appropriate. Prior to the application of parametric tests, the assumption of normality will be assessed for all continuous variables using the Shapiro–Wilk test.

For comparisons involving paired quantitative data, Student’s *t*-test for paired samples will be used when the normality assumption is met. If this assumption is violated, the non-parametric Wilcoxon signed-rank test will be applied.

For between-group comparisons (intervention vs. control), independent-sample t-tests will be used for normally distributed variables, while the Mann–Whitney U test will be used for non-normally distributed variables.

To evaluate the effect of the intervention across time and altitude conditions, a mixed-model ANOVA will be used, including group (intervention vs. control) as a between-subject factor and time (pre vs. post) and altitude as within-subject factors.

For categorical variables, McNemar or chi-square tests will be applied as appropriate.

A multivariate linear regression analysis will be performed to adjust for potential confounding variables (age, sex, BMI, and physical fitness), including group allocation as an independent variable. Model assumptions (normality, homoscedasticity, and independence of residuals) will be checked.

Statistical significance will be set at *p* < 0.05. All statistical analyses will be performed using IBM^®^ SPSS^®^ Statistics 28 software.

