### 2.3. Sample Size

Participants will be recruited using a convenience sampling approach among eligible nursing students. After baseline assessment, participants will be randomly allocated to one of two parallel groups: (1) an intermittent hypoxia conditioning group or (2) a sham control group. The random allocation sequence will be generated using a computer-based random number generator with a 1:1 allocation ratio. To ensure balance between groups, block randomisation will be applied with variable block sizes. Allocation concealment will be guaranteed using sealed, opaque, and sequentially numbered envelopes prepared by an independent researcher not involved in participant recruitment or assessment.

The assignment of participants to study groups will be conducted by a researcher not involved in outcome assessment or data analysis. Due to the nature of the intervention, participants and intervention supervisors cannot be blinded to group allocation. However, outcome assessors and data analysts will be blinded to group allocation to minimise detection and analysis bias. Specifically, outcome assessors will evaluate CPR performance using anonymised, coded data with no group identifiers, ensuring that group allocation remains concealed. The randomisation sequence generation and allocation concealment will be performed by an independent researcher, who will have no involvement in outcome assessment or data analysis.

To control for potential confounding variables, a multivariate model (multiple linear regression) will be applied. The change in Q-CC following the intervention will be considered as the dependent variable, while potential confounders (e.g., age, sex, BMI, physical fitness, and blood parameters) will be included as covariates. Interactions between these variables and altitude conditions will also be explored.

The sample size calculation is based on an expected baseline proportion of correct compressions of 52%, according to a previous study [16]. Using Epidat 4.2 software, assuming paired comparisons, a 95% confidence level, and 80% statistical power, a total of 56 participants is required to detect an increase in the proportion of correct compressions to 78%. To account for potential dropouts or non-responses, the total sample size will be increased by 10%.

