To minimise the effect of fatigue between tests, each participant will have a 24 h rest period.

Stage 3: Participants assigned to the intervention group will undergo a standardised intermittent hypoxia conditioning programme (13 sessions, 45–75 min/session), including alternating cycles of hypoxia (FiO_2_ progressively reduced from 0.14 to 0.11) and normoxia, resulting in a total hypoxic exposure of approximately 728 min. The control group will undergo a sham protocol consisting of identical session structure and duration under normoxic conditions. Three to five weekly sessions will be held according to tolerance and the iAltitude^®^ protocol [42].

Stage 4: After the intervention, all the participants (*n* = 56) will perform three uninterrupted 10 min sessions of CPR: the first at 670 (P1), the second (P2) at 3000, and the third (P3) at 5000 m asl. To minimise the effect of fatigue between tests, each participant will have a 24 h rest period [42]. The criteria for completing the different CPR tests will be determined by reaching 10 min or by the physical and/or physiological limitations of the rescuer (physical exhaustion or pain, SatO_2_ < 75).

Throughout all stages, heart rate and peripheral oxygen saturation (SpO_2_) will be continuously monitored using an ear clip pulse oximeter. The training programme instructs the participant to breathe ambient air if the SpO2 level exceeds the limit specified in Table 1 (Lim SpO2). During hypoxia tests, as well as during conditioning, a nurse and/or a doctor with experience in emergency care will be present.

To minimise potential confounding due to independent practice, participants will be explicitly instructed not to perform any additional CPR training or practice outside the study protocol during the study period.

The pre-conditioning protocol for high-altitude exposure was designed based on experience and knowledge regarding the use of normobaric intermittent hypoxia (IHT) to enhance sporting performance. To this end, the following data were collected from each participant: age, sex, height, weight, body fat percentage, sport practised (if applicable), number of weekly training sessions, time spent training, and ability to perform CPR manoeuvres in accordance with the study design.

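### In its classical form, the planned mixed-model ANOVA analyses only participants with all six CPR tests; a linear mixed model with unstructured covariance would use every available test

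*Protocol article*

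**What the plan says.** Section 2.6 of the protocol article sets the analysis of the intervention across time and altitude: "a mixed-model ANOVA will be used, including group (intervention vs. control) as a between-subject factor", with time (before and after conditioning) and altitude varying within subjects. On software it says: "All statistical analyses will be performed using IBM^®^ SPSS^®^ Statistics 28 software". It does not say which SPSS procedure will fit the model, nor what happens to a participant with a missing test.

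Section 2.4 gives six tests per person: M1 to M3 before conditioning (Stage 2) and P1 to P3 after it (Stage 4), each at 670, 3000 and 5000 m. The end of a test is "determined by reaching 10 min or by the physical and/or physiological limitations of the rescuer". Section 2.5 defines Q-CC as the mean of three percentages of compressions.

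The article expects some loss. Section 2.3 says: "To account for potential dropouts or non-responses, the total sample size will be increased by 10" per cent. Section 2.1 makes altitude intolerance, judged during CPR at simulated height, a ground for exclusion.

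**The concern.** The wording in section 2.6 is that of the classical split-plot ANOVA, which needs a full row of six values per person. Someone who misses only P3, or who leaves during the weeks of conditioning between the two sets of tests, would then contribute nothing, although three to five valid tests exist. In a trial of 56 people, which the Discussion itself calls small, that is an avoidable loss of precision on the main comparison between the groups.

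The classical analysis also needs sphericity, or a correction for it, for the terms that involve altitude.

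**Working it through.** **The plan's own figure.** Section 2.3 gives 56 participants, "assuming paired comparisons, a 95% confidence level, and 80% statistical power", with an "expected baseline proportion of correct compressions of 52" per cent rising to 78%. The share of discordant pairs is not given. I assume independent pairs and a two-sided 0.05 level.

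- Discordant share: 0.52 × 0.22 + 0.48 × 0.78 = 0.489. Difference: 0.26.
- n = (1.96 × √0.489 + 0.842 × √(0.489 − 0.26²))² / 0.26² = 54.3, so 55. A discordant share of 0.503 gives 56.

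The figure is reproducible, so 56 is a fair base. The 10% increase gives 56 × 1.1 = 61.6, so 62.

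**Complete participants under independent gaps.** If a share q of each test is missing, independently, the share with all six tests is (1 − q)⁶. The article gives no value of q, so the range is assumed.

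| q per test | (1 − q)⁶ | of 56 | of 62 |
|---|---|---|---|
| 1% | 0.941 | 52.7 | 58.4 |
| 2% | 0.886 | 49.6 | 54.9 |
| 3% | 0.833 | 46.6 | 51.6 |
| 5% | 0.735 | 41.2 | 45.6 |
| 10% | 0.531 | 29.8 | 32.9 |

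**Uneven gaps.** With 3% missing at 670 and 3000 m and 10% at 5000 m (assumed), the complete share is 0.97⁴ × 0.90² = 0.717, or 40.2 of 56. Yet (4 × 0.97 + 2 × 0.90) / 6 = 94.7% of tests exist.

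**Clustered gaps.** If instead 10% of people leave during conditioning and nothing else is missing, 5% of all tests are absent (three of six for one person in ten). Then 0.90 × 56 = 50.4 people are complete, against 41.2 when the same 5% is spread independently. A person with no post-conditioning test also adds little to a group-by-time contrast under any model. Clustering therefore shrinks both the loss and the gain from changing method.

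**What a mixed model recovers.** The simulations used 56 people, total SD 20 and the 3%/10% gaps completely at random. All of these inputs are assumed. The ANOVA test of group by time is a t-test on each complete participant's mean change. The unstructured model used 400 runs and a t reference with 54 df.

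| Setting | Complete-case ANOVA | Unstructured mixed model |
|---|---|---|
| No effect, no person-by-time variance | 5.8% rejected | 6.3% |
| No effect, person-by-time variance 100 | 3.8% | 5.3% |
| Effect 8.5 points, no person-by-time variance | 66% power | 76% |
| Effect 12 points, person-by-time variance 100 | 65% power | 80% |

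Monte Carlo standard errors are about √(0.05 × 0.95 / 400) = 1.1 points for the error rates and √(0.66 × 0.34 / 400) = 2.4 points for power.

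**A random intercept alone is not a safe substitute.** In 600 runs with person-by-time variance 100 and no effect, it rejected in 18.2% of runs, against 6.2% for the ANOVA.

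**Absence that depends on the unseen value.** With a true effect of 8.5 points and higher assumed missing rates, the mean estimates were 8.03 (ANOVA) and 7.93 (random-intercept model) in one setting, and 7.46 and 7.88 in another. Neither method removed the bias.

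**The case against.** The strongest reply is that the deletion is inferred. The article names a family of models, not a procedure. SPSS MIXED fits the same three factors on available tests, and missing-data rules are commonly left to a full protocol or SAP, neither of which is shown. This stands as a limit on the claim: the article does not say that incomplete participants will be dropped. It does not remove the point, because the method it names has that consequence in its usual form, and a better one is available in the same software.

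A reader might also infer that tests ended by exhaustion or desaturation go missing, mostly at 5000 m, so that deletion removes those who struggled most. The documents do not support this. Section 2.4 treats those limits as ways of completing a test, and Q-CC is a percentage that a shortened test still supplies. Gaps come from tests not done, withdrawal or exclusion. A person excluded for intolerance may be out under either model.

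Three further points are fair. No effect size in SD units appears in the article, so any power figure is illustrative. Sphericity does not arise for group by time, which has two time levels; it concerns only the altitude terms, where standard corrections exist. The mixed model is not free: it depends on its covariance structure and on missing at random.

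**Conclusion.** The point holds in a limited form. The ANOVA as named is a conventional and valid analysis if every participant completes six tests, and with complete data and the same covariance assumptions a mixed model gives the same estimate. With gaps, the classical form wastes valid data: about 6 to 15 of 56 people (56 − 50 to 56 − 41) at independent rates of 2% to 5% per test, fewer if gaps cluster within people. Under the assumed 3%/10% pattern, the unstructured mixed model gained 10 to 15 points of power with type I error of 5.3% and 6.3%.

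These sizes rest on assumed missing rates, SD, correlations and effects. They do not show that the trial will lose this much, that the deletion is planned, or that deletion would bias the result in a known direction. The change is still worth making, since the sample is small and the cost is low.

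**What to change.** In section 2.6, replace the mixed-model ANOVA with a linear mixed model (SPSS MIXED) fitted to all available tests:

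- Fixed effects: group, time, altitude and all their interactions.
- Within-person covariance: unstructured and prespecified, not a random intercept alone. Name a fallback structure in case the fit does not converge.
- Small-sample degrees of freedom, such as Satterthwaite or Kenward–Roger.
- Reporting: the group-by-time contrast at each altitude with its 95% CI.
- State that a test ended early contributes its Q-CC value, and which events make a test missing.
- Add a sensitivity analysis for tests absent because of exhaustion or altitude intolerance, since missing at random is doubtful there.

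If a mixed model on available tests was always intended, naming the procedure and the covariance settles most of this.

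Cost: a few sentences and a little more analysis work, with no extra data. The downsides are 6 × 7 / 2 = 21 covariance parameters to estimate from about 56 people, and reliance on missing at random.
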